### Interventions

Subjects will be randomized to one of two treatment groups. One group will receive only the EOTA intervention, the other group will receive the EOTA intervention with the addition of mechanical lumbar traction. Subjects in both treatment groups will receive a total of 12 individual physical therapy treatment sessions delivered over a 6-week treatment period. Three sessions will occur during weeks 1 and 2 of the treatment period, two sessions in weeks 3 and 4, and one session during weeks 5 and 6.

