#### Treatment Side Effects

A questionnaire for reporting any side effects the subject perceives to be related to treatment procedures will be completed by the subject at the 6-week follow-up. The questionnaire is based on a questionnaire used previously to examine subjects with LBP receiving spinal manipulation [43]. Subjects are asked if they experienced any commonly-reported side effects following treatment including stiffness, muscle spasm, fatigue, or increased radiating symptoms. Subjects will also be able to report side effects not specifically named. For each side effect reported, the subject is asked to report the time of onset relative to the precipitating treatment session (≤24 hours or >24 hours), the duration of the side effect symptoms (≤24 hours or >24 hours), and severity of symptoms (categorized from 1 "light" to 4 "severe").

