### Physical Therapist Training and Compliance

All physical therapists will be trained by the study investigators in the treatment protocols used in this study. One training session of approximately 90 minutes will be used to review all treatment procedures. Each of the participating physical therapy clinics will be equipped with the 3D Active Trac traction table prior to initiation of the study, and physical therapists will have experience with this equipment. Each participating physical therapist will also have prior experience using an EOTA intervention. Participating physical therapists will be trained to provide treatment for subjects in either group in this study. The assignment of a study subject to a participating physical therapist will be done on a pragmatic basis (location of clinic, availability of appointment, etc.) A study treatment folder will be provided to the treating physical therapist each time he or she is assigned a new study subject. The study treatment folder will include a written protocol outline specific to the subject's group assignment, and treatment forms for each physical therapy session to allow the physical therapist to record the specific activities performed during the session and the exercises assigned to the subject for home performance. In addition, each treatment session form will require the physical therapist to record the subject's reported home exercise compliance since the last treatment session. The physical therapist's compliance with the treatment protocols will be recorded and reviewed periodically. The use of any off-protocol co-interventions will be recorded. The subject's compliance with performing the assigned home exercises will be recorded from the physical therapist's treatment forms.

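### Side effects are described as collected by one self-report at 6 weeks with 24-hour timing items, although half the sessions are then about four weeks old or more; asking at each session would be a cheap improvement.

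*Protocol article*

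**What the plan says.** The section Treatment Side Effects describes one instrument. It covers "any side effects the subject perceives to be related to treatment procedures" and "will be completed by the subject at the 6-week follow-up". It names several common effects, leaves room for others, and grades severity from 1 to 4. On timing, "the subject is asked to report the time of onset relative to the precipitating treatment session", split at 24 hours, and duration is split at 24 hours as well.

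The section Interventions gives both arms "a total of 12 individual physical therapy treatment sessions delivered over a 6-week treatment period", with more sessions early than late: the figure is three for weeks 1-2, two for weeks 3-4 and one for weeks 5-6.

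Two other contacts are described, and side effects are not named for either:

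- Physical Therapist Training and Compliance provides "treatment forms for each physical therapy session to allow the physical therapist to record the specific activities performed during the session", together with the home exercises assigned and the patient's reported adherence since the previous visit.
- Outcome Measures describes monthly telephone or e-mail contact about healthcare use and lost work days.

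Side effects are not listed among the outcomes in Outcome Measures, and Data Analysis describes no between-group analysis of them.

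**The concern.** The items and the time of asking do not fit each other well. Whether stiffness began 20 or 30 hours after a given session, and whether it lasted a day, is easy to answer at the next visit. It is hard to answer at week 6, when the session is one of 12 and may lie more than a month back. Brief, mild effects are the ones most easily forgotten or placed wrongly in time.

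A single collection point also means that a patient who is not assessed at 6 weeks leaves no side-effect record at all, however many sessions were attended. Increased radiating symptoms is one of the effects the questionnaire names, and it is a plausible reason to leave a trial, so missing reports need not be a random subset.

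What is at stake is the description of tolerability in each arm. That has some weight here: the Background says the preliminary trial gave traction in the first two weeks only, whereas the overview of the design has it continuing through all six.

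**Working it through.** **1. Session schedule (Interventions).** Read as sessions per week, 3 + 3 + 2 + 2 + 1 + 1 = 12, which reproduces the stated total. Read as sessions per two-week block it would give 3 + 2 + 1 = 6, so the weekly reading is the one intended.

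**2. Age of the exposures when the questionnaire is filled in (week 6).**

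- Weeks 1-2: 6 of 12 sessions (50%), at least 6 - 2 = 4 weeks earlier.
- Weeks 1-4: 10 of 12 sessions (83%), at least 6 - 4 = 2 weeks earlier.
- Weeks 5-6: 2 of 12 sessions (17%), less than about two weeks earlier.

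**3. Ceiling on missing questionnaires (Sample Size and Power).** The article's chain reproduces: 86 x 1.2 = 103.2, given as 104; 104 / (1 - 0.13) = 119.5, so 120 are recruited. The allowance is (120 - 104) / 120 = 16/120 = 13.3%. It is not tied to the 6-week visit, so 16 patients is the most that can miss the questionnaire under that allowance, not a forecast.

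**4. What recall error could do (assumed inputs).** Let r be the risk of a side effect per session, taken as independent across sessions, and s the share of week 1-2 events that are remembered. Later events are taken as fully remembered.

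- True share of patients with any event: 1 - (1 - r)^12.
- Reported share: 1 - (1 - rs)^6 (1 - r)^6.

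| r | s | True | Reported |
|---|---|---|---|
| 2% | 0.5 | 21.5% | 16.6% |
| 2% | 0.9 | 21.5% | 20.6% |
| 5% | 0.5 | 46.0% | 36.9% |
| 5% | 0.7 | 46.0% | 40.6% |
| 5% | 0.9 | 46.0% | 44.2% |

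The shortfall runs from about 1 to 9 percentage points over these inputs.

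**5. What missing questionnaires could do (assumed rates, missing share at its ceiling of 16/120).** True rate = p_obs x (104/120) + p_miss x (16/120). With p_obs = 20%:

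- p_miss = 30%: 17.3% + 4.0% = 21.3%
- p_miss = 60%: 17.3% + 8.0% = 25.3%
- p_miss = 90%: 17.3% + 12.0% = 29.3%

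If p_miss equals p_obs there is no bias, and if it is lower the bias reverses. The article gives no value for r, s, p_obs or p_miss, overall or by arm. Steps 4 and 5 therefore show how the errors would act and are not estimates for this trial.

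**The case against.** The strongest reply is that the article condenses a fuller protocol that is not shown. Continuing adverse-event reporting is often left to such a document, and the session form itself is not reproduced, so its silence on side effects does not prove that none are recorded. This stands, and it limits the point to the method as described. It does not remove the point, because the article gives side effects a section of their own and fixes when they are asked about.

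Three stronger readings are tempting, and the article supports none of them.

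- A reader might infer that early events are lost. They are not: the questionnaire asks about effects of any session and they can be reported. The risk is poor recall.
- A reader might infer that everyone who stops treatment early is lost. The questionnaire belongs to the 6-week follow-up and not to finishing treatment, and Data Analysis keeps patients in their randomized group whatever their adherence. Only those not assessed at 6 weeks give no data.
- A reader might infer that traction will look safer than it is. That would need under-recall or loss to be greater in the traction arm, and nothing in the article shows this. In an open trial, attribution in retrospect could equally raise reports in that arm. No formal safety comparison is described that could be distorted.

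It can also be said that the questionnaire is based on one used before, whose intended recall period cannot be seen here; this stands, and no misuse of that instrument is claimed. Finally, moving the items to the session would be a poor exchange if the treating therapist, who knows the allocation, did the asking. That is a fair objection to therapist-elicited reports, and it is met if the patient completes the items.

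**Conclusion.** The point holds as a cheap improvement to a stated method. It is not an error or a contradiction in the article. As described, one retrospective self-report at 6 weeks carries items with 24-hour resolution, while 6 of 12 sessions are about four weeks old or more and 10 of 12 are about two weeks old or more. The likely result is less reliable timing and some under-reporting of brief, mild effects. In addition, at most about 16 of 120 patients would contribute nothing, assuming the whole 13% allowance is used up by week 6.

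The session figures rest only on the article's schedule read per week. The amount of under-reporting, and whether it differs between arms and in which direction, cannot be derived from the document.

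**What to change.** 1. Add a short patient-completed block to the paperwork already used at each visit. It would carry the existing items (type, onset within or beyond 24 hours, duration within or beyond 24 hours, severity 1-4) and cover the time since the previous session. The patient fills it in and the therapist does not elicit the answers.
2. For patients who stop attending, ask the same items at the existing monthly contact.
3. Keep the 6-week questionnaire for the last interval.
4. Report side effects by arm for all patients with at least one session, with the number who supplied data.
5. If the full protocol already captures side effects per session, say so in Treatment Side Effects; no other change is then needed.

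The cost is one block on existing paperwork and a minute or two per session, with no extra visits. More minor events will be recorded, and repeated asking may itself prompt reports. Using the same form in both arms, which have the same number of scheduled sessions, keeps the prompting equal.

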## Methods/Design

### Overview of research design

The study will be a randomized controlled trial comparing an extension-oriented treatment approach (EOTA) with or without the addition of mechanical traction. The study will include patients with signs and symptoms consistent with lumbar nerve root irritation. Randomization will be stratified based on the preliminary sub-grouping criteria (table 1). The study design and subject flow are outlined in figure 3. Subjects in each treatment group will receive 12 individual treatment sessions with a physical therapist delivered over a 6-week period. Patients randomized to the traction group will receive traction combined with the EOTA throughout the 6-week treatment period. Outcomes will be assessed at the conclusion of treatment (6 weeks), and after 6 months and 1 year. The study has been approved by the Institutional Review Boards at the University of Utah, Intermountain Healthcare, Inc., and Wilford Hall Medical Center.

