Subjects' utilization of healthcare resources and associated direct healthcare costs, as well as work absence due to LBP will be recorded during the year following enrollment in the trial. The subject will be contacted by phone or e-mail on a monthly basis following enrollment. At each contact the subject will asked to report any visits to healthcare providers for the management of LBP, any diagnostic (e.g., MRI, radiographs, etc.) or interventional procedures (e.g., injection, surgery, etc.), and any prescription medication purchased for LBP. The subject will also be asked to report the number of days absent from work related to LBP. Direct healthcare costs will be computed by assigning a standardized cost to each healthcare service received based on average procedure cost data from Intermountain Healthcare's health plan.

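### The two-level duration item on the 6-week side-effect form cannot separate a brief effect from one still present, when type, onset and severity are the same

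*Protocol article*

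**What the plan says.** All of this is in the protocol article.

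- **Timing of the form (Treatment Side Effects).** The questionnaire "will be completed by the subject at the 6-week follow-up". It is adapted from one used earlier in patients with low back pain who received spinal manipulation.
- **Type of effect (same section).** The prompted effects are "stiffness, muscle spasm, fatigue, or increased radiating symptoms", and patients may add others.
- **Detail per effect (same section).** The form asks for "the time of onset relative to the precipitating treatment session (≤24 hours or >24 hours"), for "the duration of the side effect symptoms (≤24 hours or >24 hours") and for severity on four levels, from light to severe.
- **Treatment period (Interventions).** Both arms receive "12 individual physical therapy treatment sessions delivered over a 6-week treatment period".
- **Other follow-up (Overview of research design; Outcome Measures).** "Outcomes will be assessed at the conclusion of treatment (6 weeks), and after 6 months and 1 year". These outcomes include the modified Oswestry score, separate back and leg pain ratings, and a global rating of change. In addition, "The subject will be contacted by phone or e-mail on a monthly basis following enrollment"; the topics listed for these contacts are care, procedures and prescriptions for low back pain, and days off work.

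**The concern.** Every participant enters with at least one sign of nerve root compression, and the experimental arm adds traction. Increased radiating symptoms is one of the prompted side effects. For that item, a central safety question is whether a worsening passed or lasted. A duration scale that stops at 24 hours does not ask this. A table of patients with effects longer than 24 hours would pool short-lived reactions with effects still present when treatment ends, and the two arms could differ in that mix without the table showing it.

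**Working it through.** The plan states no figure on this point, so there is nothing to reproduce. The check asks what the form can and cannot tell apart.

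**1. Codes available per effect type.** Onset has 2 levels, duration 2 and severity 4, which gives 2 × 2 × 4 = 16 codes. Of these, 2 × 1 × 4 = 8 carry the longer duration. None of the 8 says whether the effect has ended.

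**2. What the longer category covers.** The treatment period is 6 × 7 = 42 days, and the schedule, read as sessions per week, is 3 + 3 + 2 + 2 + 1 + 1 = 12 sessions. Assume that the form is completed on day 42 and that the effect starts at the beginning of week w. The longest duration that can be seen is then 42 − 7(w − 1) days.

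| Effect starts at beginning of | Longest observable duration | Durations sharing one code |
|---|---|---|
| Week 1 | 42 days | just over 1 to 42 days |
| Week 3 | 28 days | just over 1 to 28 days |
| Week 5 | 14 days | just over 1 to 14 days |

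These are possible ranges. The article gives no information on how often long effects occur.

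**3. What this does to a comparison of arms.** Suppose that, for one effect type, a of 60 traction patients and b of 60 comparison patients report the longer duration. From the form alone, the number still affected at 6 weeks can be anything from 0 to a in one arm and from 0 to b in the other. The difference in proportions still affected can then lie anywhere from −b/60 to +a/60. If a = b, the reported difference is zero while the true difference in ongoing effects may be up to a/60 in either direction. Each patient counts for 1/60 = 1.7 percentage points. The article gives no value for a or b, so this cannot be turned into an expected size.

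**4. Whether other data close the gap.**

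- *Type, onset and severity* separate many records, but none of them measures persistence. A severe effect may be short and a moderate one lasting.
- *Leg pain, Oswestry and global change* are collected at 6 weeks, alongside the form. A patient whose leg pain is above baseline can be seen. However, every patient enrols with recent symptoms below the gluteal fold, so later leg pain may be the original condition or a treatment-related worsening. Stiffness, spasm, fatigue and write-in effects have no dedicated measure among these outcomes.
- *Monthly contacts* would pick up a lasting effect if it led to care or time off work for low back pain. One that led to neither would not appear in the topics described.

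The gap is therefore narrowed but not closed.

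**The case against.** The strongest reply is that the form records more than duration, and that the trial follows patients closely for a year. Three stronger readings that a reader might infer do not hold.

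- *That lasting nerve-related worsening is recorded like two days of soreness.* It is not. Severe increased radiating symptoms and light stiffness differ in type and severity, and share at most the onset and duration codes. Records coincide only when type, onset and severity all match.
- *That side effects are never followed until they resolve.* The article describes no such follow-up, but it is a condensed account. Follow-up of adverse events is commonly left to the full protocol, which is not shown, so silence here is not evidence of absence. Patients' overall status is also measured again at 6 months and 1 year.
- *That effects of the last sessions are lost because the form comes too soon.* The interval between the last session and the 6-week assessment is not given. Only the final session could be affected, and only if the form is completed within about a day of it. No loss can be estimated.

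It may also be said that the form follows an earlier questionnaire, and that keeping its categories allows comparison. That is a fair reason to keep the 24-hour split available, but not a reason to record nothing finer. What stands of the reply is that the point is narrow and that the outcome data soften it. It does not answer the remaining point: the duration item is described in full, and it has no option for an ongoing effect.

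**Conclusion.** The point holds in a limited form. Among effects of the same type, onset and severity, the duration item cannot separate one that lasted 25 hours from one still present at 6 weeks, a span of up to about 42 days for an effect that began at the first session. The outcome scores fill this gap only in part, since they are not linked to the reported effect.

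This rests on the article giving the response categories completely, as its wording suggests, and on the form being completed at about day 42. It is a minor improvement to the safety data. Nothing in the plan is contradicted or miscalculated, and the primary outcome, its analysis and the sample size are unaffected.

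**What to change.** On the existing 6-week form, for each effect:

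1. Keep a box for 24 hours or less. If the effect lasted longer, ask for the number of days (for the longest episode, if it recurred).
2. Add one question: still present today, yes or no. For a yes, the days count only up to the date of the form.
3. Report by arm the number of patients with any effect still present at 6 weeks, and separately the number with increased radiating symptoms still present.
4. Collapse the answers to the 24-hour split when comparing with the earlier questionnaire.

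Optionally, for patients with an effect still present, add one question on resolution to the monthly contacts. With contacts at months 1 to 12, 12 − 1 = 11 fall after week 6. This is unnecessary if the full protocol already provides for it.

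The cost is one changed item, one added item and, if wanted, one conditional question in contacts already planned. The only drawback is a slightly altered questionnaire, and the retained 24-hour box removes most of that. The change concerns data capture only and does not touch treatment.

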### Physical Therapist Training and Compliance

All physical therapists will be trained by the study investigators in the treatment protocols used in this study. One training session of approximately 90 minutes will be used to review all treatment procedures. Each of the participating physical therapy clinics will be equipped with the 3D Active Trac traction table prior to initiation of the study, and physical therapists will have experience with this equipment. Each participating physical therapist will also have prior experience using an EOTA intervention. Participating physical therapists will be trained to provide treatment for subjects in either group in this study. The assignment of a study subject to a participating physical therapist will be done on a pragmatic basis (location of clinic, availability of appointment, etc.) A study treatment folder will be provided to the treating physical therapist each time he or she is assigned a new study subject. The study treatment folder will include a written protocol outline specific to the subject's group assignment, and treatment forms for each physical therapy session to allow the physical therapist to record the specific activities performed during the session and the exercises assigned to the subject for home performance. In addition, each treatment session form will require the physical therapist to record the subject's reported home exercise compliance since the last treatment session. The physical therapist's compliance with the treatment protocols will be recorded and reviewed periodically. The use of any off-protocol co-interventions will be recorded. The subject's compliance with performing the assigned home exercises will be recorded from the physical therapist's treatment forms.

### Data Integrity

The integrity of the data collected throughout the trial will be monitored by regular review of the data collection forms for missing responses, errors, or out of range values.

### Data Analysis

Intention-to-treat principles will be applied to all analyses, with all subjects analyzed with the group to which they were randomized regardless of compliance with treatment. Hypotheses 1 and 2 relate to determining the overall effectiveness of adding traction to an EOTA intervention. Linear mixed models with repeated measures will be used to analyze overall treatment effectiveness. The treating physical therapist and physical therapy clinic will be modeled as random effects. Covariates, treatment group, and treatment group by time interaction will modeled as fixed effects. The treatment group by time interaction effect will be used to examine hypotheses 1 and 2 related to the effectiveness of adding traction to an EOTA intervention. Treatment effect sizes with 95% confidence intervals will be calculated for each follow-up time point. The third hypothesis, examining effectiveness of adding traction to an EOTA intervention based on subjects' status on the preliminary sub-grouping criteria, will be examined with similar procedures with the inclusion of a 3-way, time by group by sub-grouping status interaction term. Statistical significance will be based on an alpha level of 0.05 for all analyses.

